#### Analysis of primary and secondary endpoints

2.12.1

Because the goal of this small exploratory study is to generate appropriately powered large-scale RCTs for future, we will perform descriptive statistics using PPS. After evaluation with descriptive statistics, for additional information, analysis of covariance including the baseline value as a covariate will be performed for comparison of groups. If the distribution is greatly skewed in a blinded review, transformation of values such as logarithmic transformation will be considered. As a sensitivity analysis of the primary endpoint, the same analyses will be performed for the PPS. All analyses will be performed with a two-sided significance level of .1.

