### Statistical considerations

2.12

The full analysis set is defined as all patients enrolled in this study, excluding cases of serious noncompliance with ethical guidelines for life sciences and medical research involving human subjects, untreated cases, and unobserved cases (ie, complete absence of the primary endpoint). The per-protocol set (PPS) is defined as the population of patients included in the full analysis set who do not meet any of the following conditions:

(1)Patients who do not meet the selection criteria specified in this protocol or who violate the exclusion criteria.(2)Significant deviations from the study protocol.(3)Patients who fail to receive sufficient anesthetics (ie, the BIS value during surgery not being lower than that before induction of anesthesia).(4)Cases of concomitant use of prohibited drugs.

The safety analysis set comprises the population of patients who receive at least 1 dose of the study drug.

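### The sensitivity analysis of the primary endpoint repeats the main analysis on the same per-protocol set, and the full analysis set is used in no efficacy analysis

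*Protocol article*

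**What the plan says.** Section 2.12 (Statistical considerations) of the protocol article defines three sets.

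- **FAS:** "The full analysis set is defined as all patients enrolled in this study, excluding cases of serious noncompliance with ethical guidelines", and excluding also "untreated cases, and unobserved cases (ie, complete absence of the primary endpoint".
- **PPS:** "the population of patients included in the full analysis set who do not meet any of the following conditions". The four conditions are a breach of eligibility, a major protocol deviation, insufficient anaesthesia and use of a prohibited drug. The third is worded "Patients who fail to receive sufficient anesthetics (ie, the BIS value during surgery not being lower than that before induction of anesthesia".
- **Safety set:** patients given at least one dose of study drug.

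Section 2.12.1 then sets out the efficacy analyses in this order.

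- With the exploratory aim given as the reason, "we will perform descriptive statistics using PPS".
- As additional information, "analysis of covariance including the baseline value as a covariate will be performed for comparison of groups". This sentence names no set.
- Finally, "As a sensitivity analysis of the primary endpoint, the same analyses will be performed for the PPS".

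Section 2.12.2 puts the adverse event comparison on the safety set.

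**The concern.** A sensitivity analysis should change something, here the analysis population, and show whether the result moves. This one changes nothing. The presence of a defined but unused FAS suggests that one of the two sentences was meant to name it. As the text stands, the population for the primary endpoint is open to doubt, and the choice could be settled after the data are seen.

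The set matters because three of the four PPS conditions arise after randomisation. The BIS condition is a response to the allocated sedative, and deviations and prohibited drugs occur during or around treatment in a trial that section 2.2 describes as open. Exclusions of this kind can differ between arms in number and in the type of patient removed.

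The exploratory aim raises the stake in one respect. Sections 2.10 and 2.12.1 both give the trial's purpose as informing a larger trial, so the estimates themselves are its main product. If that trial is analysed as randomised, an estimate available only from the PPS is the wrong planning value.

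**Working it through.** The document states that no sample size calculation was done, so there is no figure of the plan to reproduce. The check is to trace which set each analysis uses.

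| Analysis | Section | Set |
|---|---|---|
| Descriptive statistics, primary and secondary endpoints | 2.12.1 | PPS, stated |
| Analysis of covariance between groups | 2.12.1 | none named; PPS from context |
| Sensitivity analysis, primary endpoint | 2.12.1 | PPS, stated |
| Adverse event comparison | 2.12.2 | safety set, stated |

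**Step 1. Is the sensitivity analysis different from the main one?** The first and third rows name the same set, and the third row calls for the same analyses. For the descriptive statistics the duplication is explicit. For the analysis of covariance it follows if that analysis also uses the PPS, which is the natural reading because no other set is introduced between the two PPS sentences.

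**Step 2. Where is the FAS used?** It is mentioned twice, both times in section 2.12: in its own definition and as the parent of the PPS. No row of the table uses it.

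**Step 3. Which PPS conditions depend on events after randomisation?** Deviations, the BIS criterion and prohibited drugs do. The eligibility condition concerns the patient's status at entry.

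**Step 4. Can the effect be sized?** Let an arm have n patients in the FAS, of whom d are not in the PPS. With M_in the mean recall of those kept and M_out the mean of those dropped,

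PPS mean − FAS mean = M_in − [(n − d) × M_in + d × M_out] / n = (d / n) × (M_in − M_out).

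The documents give n = 35 per group as the target (section 2.10) and a score from 0 to 4 posters (section 2.7.1). They give neither d, M_in nor M_out. All that follows is a ceiling: each dropped patient can move an arm mean by at most 4 / 35 = 0.11 posters, up or down, if all 35 are in the FAS. The actual shift, and its sign, cannot be computed.

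**The case against.** The strongest reply is that this is a slip of wording in a condensed article. A sensitivity analysis on the same set makes no sense as a design, so one PPS should read FAS, and the full protocol or an analysis plan may have it right. The trial is exploratory, descriptive statistics come first, and no confirmatory claim hangs on the choice of set. The slip is likely, and the exploratory aim does lower the consequence. But the article does not leave a detail out; it states a rule that defeats itself. Nor does it show which mention is wrong. The first carries a reason, so a PPS main analysis with an FAS sensitivity analysis would also remove the duplication.

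Several stronger readings are tempting, and the documents do not support them.

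- A reader might infer that no result at all escapes the PPS exclusions. The adverse event comparison uses the safety set, so the point is limited to efficacy.
- A reader might infer that moving to the FAS restores the groups as randomised. This FAS omits untreated patients, those with no primary endpoint and those with serious ethical noncompliance. It is a modified intention-to-treat set, closer to the randomised groups but not the same.
- A reader might infer that unblinded investigators decide who is excluded. The documents do not say who records or judges these events, and section 2.9 states that data and outcome assessors are blinded. Blinded assessment of recall does not, however, make the exclusions independent of treatment.
- A reader might expect many BIS exclusions. Section 2.3 adjusts both drugs with reference to BIS, so few are likely. Deviations and prohibited drugs remain as routes.
- A reader might go on to say by how much the next trial would be mis-sized. With no exclusion count, standard deviation or expected effect in the document, any such ratio would be pure assumption.

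**Conclusion.** The point holds. As written, the sensitivity analysis of the primary endpoint repeats the main analysis on the same patients and carries no information, and no efficacy analysis is assigned to the FAS. For the descriptive statistics this rests on the stated text alone; for the analysis of covariance it rests on reading the PPS as its set. The efficacy results would then all exclude patients for events after randomisation in an open trial. Whether this biases the comparison, in which direction and by how much, is unknown. It would be nil if no one were excluded. What is certain is that the plan's own robustness check could not reveal it, and that the text must be reconciled before analysis.

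**What to change.** Reconcile sections 2.12 and 2.12.1 so that the primary endpoint is analysed in the FAS by randomised group.

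- **Preferred:** analyse the primary and secondary endpoints in the FAS by randomised group, naming the FAS for both the descriptive statistics and the analysis of covariance, and keep the PPS for the sensitivity analysis of the primary endpoint. Each defined set then has a job.
- **Minimum:** if the PPS is kept as the main set, run the sensitivity analysis in the FAS.
- In either case, fix PPS membership before recall scores are seen, and report the FAS estimate as the planning value for the confirmatory trial.
- State that the FAS leaves out the three groups named in section 2.12, and report how many patients each exclusion removes per arm.

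The cost is one or two sentences, with no new data or patients. The reported estimate may be slightly less favourable than the PPS one.

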#### Safety analysis

2.12.2

The subject of this analysis will be the safety analysis set. The incidence of each AE (hypotension, bradycardia, rhabdomyolysis, and anaphylaxis) will be compared between the anesthesia groups using the χ-square test or Fisher exact test.

### Monitoring

2.13

This research will be periodically monitored to ensure that the study is conducted safely and in accordance with the implementation plan as well as to determine if data are being recorded accurately and stored properly.

### Ethics approval and consent to participate

2.14

This trial is being conducted at Kyushu University in Japan. The study has received approval from the ethics review board at the Kyushu University School of Medicine Hospital Institutional Review Board (IRB approval number: 20212006) and will be conducted in accordance with the World Medical Association Declaration of Helsinki and its later amendments. All participants will be required to sign a written consent form prior to participation. Before consent is obtained, the investigators will provide an oral explanation of the study to each participant. Participation is voluntary, and patients’ privacy will be protected. The participants will be informed of their right to withdraw from this study at any time, and that this will not affect their clinical care. If this study poses a serious health risk to a participant, compensation will be provided. The study results will be published in a peer-reviewed journal and will be presented at national and international conferences.

## Discussion

3

This manuscript presents a protocol for an exploratory, randomized, open, propofol-controlled, single-center clinical trial that will be conducted to investigate the effect of remimazolam on postoperative memory retention and delayed regeneration in breast surgery patients. To our knowledge, this is the first study to elucidate the effect of remimazolam on anterograde amnesia. The study results, if confirmed, will be valuable for bedside physicians because there are few reports on remimazolam administration in clinical settings, especially for general anesthesia.

Anterograde amnesia effects of anesthetics are sometimes useful for patient comfort and can be used in various clinical situations. In contrast, this study will focus on memory. Hence, the cutoff for age was defined at <65 years. Benzodiazepine is associated with retrograde amnesia for a brief period and with respect to visual and event memory.^[9]^ Thus, we evaluated retrograde amnesia as a secondary endpoint. Additionally, when remimazolam is used in future endoscopy examinations at outpatient clinics, time to full awakening (as a safety evaluation) may be an indicator of length of hospital stay. This trial will help inform the development of future large-scale RCTs investigating the effects of remimazolam on postoperative memory retention and will thus help inform research directions, medical guidelines, and medical decision-making.

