### Study design

2.2

The standard protocol items for randomized trials guidelines were followed. The present study is an exploratory, open, propofol-controlled, single-center, randomized controlled trial (RCT) to compare the efficacy and safety of remimazolam with propofol. The study will be conducted by the Department of Anesthesiology and Critical Care Medicine, Kyushu University Hospital. In total, 70 patients aged 20 to 65 years will be randomly assigned to receive remimazolam or propofol as sedative anesthetic agent. The participants will be randomly divided into 2 groups using stratified block randomization. The study design is summarized in Figure 1 and available at URL (https://upload.umin.ac.jp/cgi-open-bin/ctr_e/ctr_view.cgi?recptno=R000052026)).

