### Inclusion criteria

2.4

The following criteria are necessary to meet eligibility requirements for the current study.

(1)Patients must provide written informed consent of their own free will.(2)Patients must be aged ≥20 years and must be <65 years.(3)Patients must be undergoing breast surgery under general anesthesia.

In breast surgery cases, intraoperative techniques are relatively uniform, and there are slight individual differences in the degree of invasion. This is because the dosage of analgesics and sedatives does not vary greatly. Although the study will be conducted only in women, there were no reports of differences in memory retention between men and women. Therefore, priority was given to unification of the degree of invasion.

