#### Primary endpoint

2.7.1

The primary endpoint to be examined in this RCT is the assessment of anterograde amnesia. This will be examined as the number of posters remembered among 4 posters 24 hours after surgery (see Figure S1, Supplemental Digital Content, which illustrates the pictures) shown after awakening from anesthesia. Specifically, after awakening from anesthesia and being able to say their names, patients are to be shown 4 posters.^[6]^

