### Randomization

2.8

An allocation supervisor appointed by the Data Center of the ARO Clinical Research Promotion Department of Clinical and Translational Center has prepared an allocation table for the purpose of randomization. The electronic data capture software used in this study refers to this allocation table for randomly allocating patients. The allocation ratio was set at 1:1. The detailed procedure of random allocation has not been provided to the researchers. The permuted block randomization block method will be used for allocation.

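### Age is treated as relevant to memory for eligibility but is not named in the group comparison, which forgoes a modest and cheap gain in precision

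*Protocol article*

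**What the plan says.** The Discussion (section 3) explains the upper age limit: "this study will focus on memory. Hence, the cutoff for age was defined at <65 years". Section 2.4 sets the range: "Patients must be aged ≥20 years and must be <65 years".

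Section 2.12.1 puts descriptive statistics first. A model follows, introduced with the words "After evaluation with descriptive statistics, for additional information": "analysis of covariance including the baseline value as a covariate will be performed for comparison of groups". No other covariate is named. The same section sets the test level: "All analyses will be performed with a two-sided significance level of .1".

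The primary endpoint (section 2.7.1) is the "number of posters remembered among 4 posters 24 hours after surgery". These posters are first shown once the patient has woken from anaesthesia.

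Allocation is described twice. Section 2.2 says "The participants will be randomly divided into 2 groups using stratified block randomization" but names no factor. Section 2.8 says "The permuted block randomization block method will be used for allocation" and mentions no strata. Section 2.10 gives 35 patients per group, chosen for feasibility, with no sample size calculation.

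**The concern.** The protocol uses age as a reason to restrict entry because the outcome is memory, and it still leaves a 45-year span among those admitted. It then specifies a model for the memory comparison in which age does not appear. Eligibility depends on age, so the variable is complete and fixed before treatment.

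The covariate that is named does not obviously do the same job. The four posters are new to the patient after awakening, so no pre-treatment value of that score exists. What the baseline value means for the primary endpoint is a separate question. It matters here only because, as written, the model may contain no prognostic variable for the primary endpoint.

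Two things are at stake, both modest. Any variation in recall that follows age stays in the error term. And a chance age difference between two arms of 35 moves the unadjusted difference in recall. The trial is meant to inform a larger one, so a tighter estimate of the group difference has some value.

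**Working it through.** **The plan's own figure.** 2 × 35 = 70, which agrees with section 2.10. No effect size, standard deviation or power is stated, so nothing further can be reproduced.

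**Inputs from the protocol.** n = 35 per group; two-sided level 0.10; age 20 to under 65.

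**Assumptions.** The documents give neither the share of recall variance explained by age within arm (R²) nor the spread of age. I take R² from 5% to 15%, that is a correlation of √0.05 = 0.22 to √0.15 = 0.39, and show smaller values too. All 70 patients are taken as analysed.

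**Step 1: precision.** Adding one covariate multiplies the variance of the group difference by (1 − R²). Estimating its slope costs a factor of about 1 + 1/(2n − 4) = 1 + 1/66 = 67/66 = 1.0152. The net ratio of standard errors is √[(1 − R²) × 67/66], and the equivalent number of patients is 70 / [(1 − R²) × 67/66].

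| R² | SE ratio before cost | SE ratio net | Equivalent N, net |
|---|---|---|---|
| 0 | 1.000 | 1.0075 | 69 |
| 0.05 | 0.975 | 0.982 | 73 |
| 0.10 | 0.949 | 0.956 | 77 |
| 0.15 | 0.922 | 0.929 | 81 |

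Over the assumed range the standard error falls by about 2% to 7%.

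**Step 2: break-even.** The ratio equals 1 when 1 − R² = 66/67, so R² = 1/67 = 0.015 and the correlation is √0.015 = 0.12. Below that the adjustment loses slightly, at most 0.75% of the standard error when age explains nothing.

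**Step 3: power, for illustration only.** Power is Φ[d / (SE ratio × √(2/35)) − 1.645], with d in SD units. At an assumed d = 0.6 the unadjusted power is 80.7%. Net of the covariate cost it becomes 80.5%, 81.5%, 83.3% and 85.8% for correlations of 0.1, 0.2, 0.3 and 0.4.

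**Step 4: chance imbalance if age is not a stratification factor.** The difference in mean age between arms, in age-SD units, has standard deviation √(2/35) = 0.239. It exceeds 0.25 SD in either direction in about 30% of trials and 0.5 SD in about 3.6%. With an assumed age SD of 10 years, the standard deviation of the difference is 10 × 0.239 = 2.39 years, and a gap of 4 years or more occurs in about 9% of trials. An imbalance of 0.239 SD moves the unadjusted recall difference by correlation × 0.239: 0.22 × 0.239 = 0.05 SD of recall at R² = 5%, and 0.39 × 0.239 = 0.09 SD at R² = 15%. If age is a stratification factor, these imbalances are smaller.

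**The case against.** The case against is fair in several respects.

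- **No contradiction.** Restricting age is itself a way of dealing with age, and patients with impaired cognition are also excluded (section 2.5). Excluding people of 65 and over does not assert a gradient in recall between 20 and 64. This stands: the passages are compatible, and the point is about efficiency.
- **Covariate lists often sit in the analysis plan.** This stands in part. The full protocol or analysis plan may add covariates. But section 2.12.1 does state a model and a covariate, so the point concerns a stated choice and not mere silence.
- **The model is supplementary.** This stands. Adding age leaves the descriptive means and standard deviations unchanged; only the between-group comparison gains.
- **The gain is assumed and small.** This stands. It depends on a correlation that the documents do not give.

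A reader might infer that the comparison is biased or its error rate inflated without age. Neither follows: randomisation protects both, and chance imbalance is already reflected in the unadjusted standard error. A reader might also infer that protection against age imbalance has been lost. The documents do not show this, because section 2.2 calls the allocation stratified without naming the factors, and age could be one of them. If it is, the analysis should include age in any case. Moreover, section 2.12.1 puts the descriptive and sensitivity analyses on the per-protocol set, which drops patients after randomisation, so balance at allocation need not carry over fully. The supportable statement is that balance on age is not assured.

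**Conclusion.** The point holds as a minor, inexpensive improvement and not as an error. The protocol regards age as relevant to memory, has it for every patient before randomisation, and does not name it in the model that compares recall.

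If age explains 5% to 15% of recall variance, adjustment is worth the equivalent of about 3 to 11 extra patients on 70. It would be wrong to call this gain free: if age explains less than about 1.5% of the variance, adjustment costs a little. The balance of a possible gain of several percent against a worst case under 1% favours naming age in advance. In an open-label trial, a covariate chosen after the results are seen would also carry less weight.

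The conclusion rests on the assumed R² range, an approximately linear relation with age, and all 70 patients being analysed.

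**What to change.** In section 2.12.1, prespecify age at enrolment, as a continuous covariate, in the supplementary between-group model for two outcomes: the primary poster count and the count of pre-anaesthesia events recalled (section 2.7.2). The yes/no item in section 2.7.2, recall of the poster shown before induction, does not suit a linear model; if age is included there, use a model for a binary outcome. Report the unadjusted group difference beside each adjusted one. If age turns out to be a stratification factor, the same wording serves.

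The cost is one line of text and one degree of freedom per model. No new data are needed.

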### Trial status

3.1

The protocol version presented here is version 1.0 from August 30, 2021. The trial is currently in the participant recruitment stage, which begins on October 13, 2021. Recruitment is expected to be completed by March 31, 2022.
